### 2.2. Participants

The following inclusion criteria will be applied: being diagnosed with idiopathic Parkinson's disease by a neurologist based on definitive evidence of responsiveness to levodopa at the start of the disease and the history of progressive hypokinesia with asymmetric onset. PD will be diagnosed based on Parkinson's Disease Society Brain Bank (PDSBB) criteria, as described in Hughes et al. (1992): age between 40 and 70 years, with no distinction for sex, schooling level or other sociodemographic characteristics; disease staging between 1.5 and 3, according to the modified Hoehn and Yahr scale (Hoehn and Yahr, 1998); undergoing regular pharmacological treatment with levodopa (equivalent dose > 300 mg) or taking antiparkinsonian medication, such as anticholinergics, selegiline, dopamine agonists, and COMT (catechol-O-methyl transferase) inhibitors for at least 4 weeks prior intervention; score of more than 24 points on the Mini-Mental State Examination (Folstein et al., 1975); not exhibiting other associated neurological diseases; and no musculoskeletal and/or cardiorespiratory changes that could compromise gait. The exclusion criteria will be diagnosis of atypical Parkinson's disease; neuropsychiatric comorbidities; convulsions, metal clips and/or pacemaker; deep brain stimulation implant; history of epilepsy; neurosurgery; traumatic brain injury; alcohol abuse or drug dependency; associated diseases of the peripheral or central nervous system; undergoing physical therapy at another location; inability to walk 10 meters; presence of important dyskinesia that prevents the participant from sitting in a chair; abnormal and persistent increase in systemic blood pressure before or during training, after three measurements taken 5 min apart-Cut-off: systolic blood pressure ≥ 140 mm Hg and/or diastolic ≥ 90 mm Hg (Malachias et al., 2016); not understanding any of the training protocol stages; chemical scalp treatment within the previous 30 days, and experiencing severe pain and/or discomfort that precludes performing the proposed activities.

History of falls in the last 12 months will be used to classify individuals into “non-fallers” (number of falls ≤ 1) or “recurrent fallers” (number of falls ≥ 2). Freezing of gait episodes will be screened and classified according to the dual-task screening questionnaire (Strouwen et al., 2014).

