### 2.5. Attrition and Adherence

Attrition will be considered in case of: two consecutive absences or three alternate absences during the training sessions; changes in medication throughout the intervention; missing post-intervention or follow-up evaluations; illness that blocks continuity in the study. Adherence strategies will be used, such as telephone contact with participants, in order to remind them of the evaluation and intervention sessions. The hours offered will be flexible and possible problems that may interfere with the participation and continuity in the intervention will try to be prevented or resolved.

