### 2.11. Data Analyses

The Statistical Package for the Social Sciences (SPSS), version 27.0, will be used in data analysis and a 5% alpha (*P* < 0.05) will be established.

The groups will be compared using the Student's *t*-test or Mann-Whitney test, for continuous variables, or the chi-squared test for categorical variables, according to the normality distribution, analyzed using the Shapiro-Wilk test. The primary outcome will be examined with a repeated measures split-plot ANOVA, with one dependent and two independent variables: one intragroup (time, with 3 levels: T0, T1 and T2), and one intergroup (a group with two levels: CG and EG) using Sidak's *post hoc* test. Analyses of covariance (ANCOVA) will be used to identify significant intergroup differences applying T0 scores as covariables. Linear regression will be used to identify response predictors. The independent variables will be group and clinical response, that is, the minimal clinically important difference (MCID). An intention to treat analysis will be conducted.

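### The intention-to-treat statement is not reconciled with the attrition rule, an exclusion criterion that can be met during training, and a primary ANOVA that needs all three visits

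*Protocol article*

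**What the plan says.** **Analysis population.** Section 2.11 (Data Analyses): "An intention to treat analysis will be conducted". The article does not define the set further.

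**Primary method.** Same section: "The primary outcome will be examined with a repeated measures split-plot ANOVA, with one dependent and two independent variables", the within-subject one being "one intragroup (time, with 3 levels: T0, T1 and T2"). The software is SPSS 27. An ANCOVA is also planned, which "will be used to identify significant intergroup differences applying T0 scores as covariables".

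**Attrition.** Section 2.5 lists as attrition "two consecutive absences or three alternate absences during the training sessions; changes in medication throughout the intervention". The same list contains missed post-intervention or follow-up assessments and illness that prevents continuation.

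**Exclusion criteria.** Section 2.2 includes a persistent blood-pressure rise found either ahead of training or in the course of it. It also includes "not understanding any of the training protocol stages", with no timing given.

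**Sample size.** Section 2.10 requires at least 46 patients for 90% power and recruits 56 (28 per group) to allow for losses. No loss rate is stated.

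**The concern.** Intention to treat means that every randomised participant is followed where possible and analysed in the allocated arm, whatever their attendance or later treatment. Section 2.5 puts two different things in one list: people who could not be measured, and people who missed sessions or changed medication but can still perform a Timed Up and Go test. Treating the second kind as lost is what intention to treat is meant to prevent. The blood-pressure criterion can be met after allocation, and the article does not say what then happens to the participant's follow-up and data.

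The primary model adds a separate problem. A classical split-plot ANOVA, as the SPSS repeated-measures procedure runs it, uses only participants with all three visits. Someone seen at T1 but not at T2 contributes nothing, although their post-intervention value is valid.

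At stake is who counts in the primary comparison of a 56-patient trial. If those who fall out differ in outcome between arms, the comparison is no longer protected by randomisation. Participants who are not assessed cannot be recovered at the analysis stage.

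**Working it through.** **1. The plan's own figures.** The 46 cannot be reproduced, because section 2.10 gives no effect size, SD or correlation. Solving backwards for a two-sample t-test with 23 per arm, two-sided 5% and 90% power gives a standardised difference of 0.977. The step from 46 to 56 is reachable by ordinary inflation: 46/(1 − 0.17) = 55.4, rounded up to 56, or 46 × 1.20 = 55.2, rounded up to 56. No error is shown there. The implied tolerated loss is (56 − 46)/56 = 17.9%.

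**2. Who section 2.5 counts as lost.** Training has 12 sessions. Two consecutive absences can leave 10/12 = 83% attended, and three separate absences 9/12 = 75%. Both kinds of participant are available for assessment at T1 and T2.

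**3. What the split-plot ANOVA keeps without imputation.** Assume that T0 is complete and that each of T1 and T2 is missed independently with probability p (assumed; the article gives no rate). The fraction kept is (1 − p)².

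| p per visit | fraction kept | of 56 |
|---|---|---|
| 5% | 0.9025 | 50.5 |
| 10% | 0.81 | 45.4 |
| 15% | 0.7225 | 40.5 |

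At p = 10%, 0.9 × 0.1 × 56 = 5.0 participants have T1 but not T2. Another 5.0 have T2 but not T1, and 0.01 × 56 = 0.6 have neither. A model using all available values would draw on 56 − 0.6 = 55.4 participants, against 45.4 for the ANOVA. If instead the same 10% missed both visits, the ANOVA would keep 0.9 × 56 = 50.4, and using all available values would recover nobody.

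**4. Power.** With the back-solved difference of 0.977, power is 94.9% with 28 per arm, 90.0% with 23, 87.1% with 21 and 81.3% with 18. Loss of the size in step 3 therefore costs little power. The larger issue is selection.

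**5. Selection, on assumed inputs.** Take no true effect, with 17.9% lost in each arm. Loss is random in the control group. In the experimental group it is likelier for worse outcomes, with a log-odds slope b per SD. The bias is the mean of those retained in the experimental group. The rejection rate is 1 − Φ(1.96 − |bias|/SE) + Φ(−1.96 − |bias|/SE), with SE = √(2/23) = 0.295.

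| slope b | bias (SD) | rejection rate |
|---|---|---|
| 0 | 0.00 | 5.0% |
| 0.5 | 0.09 | 6.0% |
| 1 | 0.16 | 8.2% |
| 2 | 0.24 | 12.8% |

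A separate simulation of 6,000 null trials with 28 per arm used unequal numbers lost, with worse scores likelier to be lost (log-weight 0.5 to 1 per SD). Removing 8 experimental and 2 control participants gave a bias of 0.13 to 0.21 SD and a type I error of 7.6% to 12.8%. Removing 7 and 3 gave 0.08 to 0.14 SD and 6.3% to 8.8%. The two approaches agree in order of magnitude. With 5 lost per arm under the same mechanism, the bias is zero by symmetry. If the excess loss were in the control group, the sign would reverse.

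**The case against.** A reader might infer that the plan contradicts itself, that its primary result would necessarily be a completer analysis, and that the error would favour the experimental group. The text does not support this.

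- Section 2.5 says what counts as attrition. It does not say that these participants leave the analysis set, stop being assessed or are replaced. Section 2.11 can be read as settling who is analysed.
- Intention to treat with imputation before the ANOVA is compatible with the article. The missing-data method may stand in a fuller protocol or analysis plan that is not shown, so its absence here is not a finding.
- The exclusion criteria are not tied to the time after allocation. The blood-pressure criterion covers both periods, and both arms train on the treadmill. The comprehension criterion sits in an eligibility list and could be applied at screening. Only the experimental group has graded dual tasks, but that the criterion would act mainly there is conjecture.
- The T0-adjusted ANCOVA at T1 needs only T0 and T1, so the plan as a whole need not discard those values.
- The bias figures rest wholly on assumed loss patterns that differ between arms.

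All of this stands, and it limits the point to a failure to reconcile the provisions. It does not remove the point. Imputation would deal with missed visits, but it would not settle whether people classed as attrition, or meeting a criterion during training, are still assessed and analysed. The sentence on the primary outcome also names the ANOVA, not the ANCOVA.

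**Conclusion.** The concern holds in limited form and should be fixed. The intention-to-treat statement is not reconciled with the attrition rule or with the criterion that can be met during training. The primary model as named does not deliver intention to treat unless values are imputed first, and without imputation it discards valid T1 data from anyone missing only T2.

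On size, only the 17.9% allowance follows from the document, and it is back-calculated. The figure of about 45 of 56 assumes independent 10% losses at each visit. Bias of roughly 0.1 to 0.2 SD and type I error of roughly 6% to 13% assume outcome-related loss that differs between arms. They show what could happen and are not predictions for this trial.

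**What to change.** 1. In section 2.5, separate adherence deviations (absences, medication changes) from loss to follow-up. Continue to assess participants with such deviations at T1 and T2, and analyse them in the arm to which they were randomised.
2. Reconcile sections 2.2, 2.5 and 2.11, so that anyone who stops training or meets a criterion after randomisation stays in follow-up and in the analysis set. This concerns data collection and analysis only; the clinical rule itself is left as it is.
3. Replace the split-plot ANOVA with a linear mixed model for all available T1 and T2 values, with T0 as covariate and group-by-visit terms. It draws no outcome information from someone missing both visits, so it complements continued assessment and does not replace it.
4. Keep the attendance-based set as a per-protocol sensitivity analysis.

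The cost is some wording, a few more assessments of participants who stop training, and possibly a less favourable estimate. SPSS 27 already has a mixed-model procedure. The change should be made before outcome data are seen.

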## 3. Discussion

Progressive cognitive compromise in PD is considered a significant predictor of disability (Yogev-Seligmann et al., 2008) and an important cause for the decline in motor function (Lemes et al., 2016). This study aims at assessing the effectiveness of dual-task training and gait training conducted concomitantly with the neuromodulation protocol In addition, we intend to analyze the clinical factors and variability between individuals that could interfere in the training of a specific task and influence the therapeutic effect, acting as response predictors of the motor and cognitive function of people with PD.

### 3.1. Cortical Activity Shift in Parkinson's Disease

The preparation and selection of movement depends on the connective dynamics of the neural network between the prefrontal cortex and the lateral premotor cortex, compatible with the context-dependent role of the activity guided externally by the lateral premotor loop (Lemes et al., 2016). Greater activation of this loop in the executive function was demonstrated when the study of neuroimaging analyzed processing speed during the finger-tapping cognitive task in participants with Parkinson's disease in the off state (Palavra et al., 2013).

In individuals with PD, executive function (EF) deficiency, related to attention and a set-shifting change in focus is associated with gait dysfunctions when challenges involve a dual-task (DT). Given this condition (DT), neural network activation, consisting of the lateral premotor loop, becomes the compensatory attribution that externally guides the movement executed (Palavra et al., 2013).

### 3.2. Dual-Task and Its Relationshiap With Executive Function

The direct relationship between bradykinesia and mental flexibility and operational memory sustains the premise that EF in PD is correlated with motor function (Domellöf et al., 2011) and becomes a strong correlation as the disease progresses (Ebersbach et al., 2013).

Cognitive demand is considered a concurrent effort while people with PD and motor fluctuations walk (Hobson and Meara, 2004; Rochester et al., 2007; Plotnik et al., 2009; Michely et al., 2015). On the other hand, DT induces an increase in cholinergic activity in the dorsolateral prefrontal cortex, thalamus and basal ganglia (Yogev et al., 2005), which makes DT training important despite the greater risk of falling.

### 3.3. Relationship Between Executiva Function and Gait

Dysfunction in planning skills may result in poor choices and unnecessary effort for people with PD to reach a destination, once the functions linked to self-regulated processing, self-awareness and rational processes are mediated by the dorsolateral prefrontal cortex (Homan et al., 1987).

Complex cognitive tasks cause exponential harm to the gait parameters of this population (Plotnik et al., 2009), which makes these tasks relevant in changing the impact of cognitive demand on locomotion (Hackney and Earhart, 2010). Preparing meals and shopping in outdoor markets have an impact on self-awareness, and the ability to walk safely and efficiently, situations that characterize dysfunction in executive function (EF) (Yogev-Seligmann et al., 2008).

Cognitive training is an effective intervention strategy to improve the working memory, processing speed and EF of people with PD [64]. It is suggested that a training protocol be implemented using a clinical approach that increases EF in terms of memory and visuospatial function (Plotnik et al., 2011), as described in the dual task training proposed here.

The trail making test (TMT) keep a direct relationship between EF and gait speed/stride length changes (Hackney and Earhart, 2010). This test analyzes cognitive flexibility, demonstrating a direct association between complex gait situations and their scores in drawing lines that connect consecutive numbers and letters (Plotnik et al., 2011).

EF changes in PD can be identified using a series of tests, once no single test is able to predict subcortical dementia syndrome (Leung et al., 2015) as PD progresses. Abstract reasoning, measured using the Wisconsin card classification test (WCST) (Leung et al., 2015), requires an understanding of the logical principles of the problem (Nocera et al., 2010), and has shown to be a marker of executive dysfunction in PD (Beatty et al., 2003). Semantic memory, which is related to the ability of recalling memorized information and EF processing, with an emphasis on thought organization, is assessed using the verbal fluency test (Berg, 1948). Attention, screened by the speed in naming color words and the colors of incongruent words, is measured by the Stroop test (Lezak et al., 2004).

The difficulty in performing daily activities that require cognitive processing and simultaneous motor demand underscores the importance of DT training in improving the EF of people with PD (Brauer and Morris, 2010; Strouwen et al., 2014; Geroin et al., 2018).

In this respect, the dual-task locomotion test with the serial subtraction of 7 is useful (primary outcome) and will help define the executive function profile of the population under study. Other tests that analyze the effect of DT as a concurrent task on locomotion will contribute to the discussion of the data.

Combining tDCS as a rehabilitation intervention is a way to enhance motor training, given that modulation of the dorsolateral prefrontal cortex (DLPFC) may improve executive control (Lange et al., 2018). Applying anodic tDCS to F3 associated with cognitive training reduced the depressive symptoms reported by people with PD even after 3 months without intervention, demonstrating the effectiveness of cognitive training alone in increasing language, attention and executive function performance (Doruk et al., 2014; Manenti et al., 2018). However, it has yet to be established which patients respond better to noninvasive neuromodulation or how the association between different therapies, such as motor or cognitive training, responds when applied in conjunction with cortical modulation using tDCS (Rodrigues et al., 2008; Cools et al., 2010; Sale et al., 2015).

This is the first study that will compare the effect of two interventions associated with motor and cognitive tasks and noninvasive neuromodulation in a same treatment protocol. We hypothesize that after adding specific tasks that stimulate cognitive processing, the group that will undergo dual task training will exhibit improved cognition and motor function. Moreover, this study will contribute to better understanding neural substrates adjacent to cognitive training involved in the execution of the DT, and identify the response predictors of the proposed training, once it includes a detailed assessment of motor and cognitive aspects of patients with PD.

## Limitations and Advantages

Additional limitations should be noted. The estimated sample size may be limited. Nevertheless, our exploratory study is a step in the direction of large-scale studies. Furthermore, the study design enables secondary between-group analyses regarding baseline variables and predictors of treatment response. Finally, the study will provide robust results regarding the isolated and combined effects of tDCS and motor training.

## Ethics Statement

The studies involving human participants were reviewed and approved by Comitê de Ética em Pesquisa do Centro de Ciências da Saúde da Universidade Federal da Paraíba–CEP/CCS-(CAAE: 30668420.7.0000.5188; Parecer no:4.003.244). The patients/participants provided their written informed consent to participate in this study.
